## Abstract

**Design:**

The CapRI study is an open, controlled, prospective, randomised multi-centre phase III trial. Patients in study arm A will be treated as outpatients with 5-Fluorouracil; Cisplatin and 3 million units Interferon alpha-2b for 5 1/2 weeks combined with external beam radiation. After chemo-radiation the patients receive continuous 5-FU infusions for two more cycles. Patients in study arm B will be treated as outpatients with intravenous bolus injections of folinic acid, followed by intravenous bolus injections of 5-FU given on 5 consecutive days every 28 days for 6 cycles. A total of 110 patients with specimen-proven R0 or R1 resected pancreatic adenocarcinoma will be enrolled. An interim analysis for patient safety reasons will be done one year after start of recruitment. Evaluation of the primary endpoint will be performed two years after the last patients' enrolment.

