## Background

Only 10–20% of patients with pancreatic cancer can be resected with curative intent at the time of diagnosis. Loco-regional recurrence and/or metastatic disease develop in the majority of patients who undergo pancreatic resection. Relapse occurs within 9–15 months after initial presentation and patients have median life expectancies of only 12–15 months without adjuvant therapy. The 5-year survival rate of patients with resected pancreatic adenocarinoma is approximately 20% [1]. The statistics for the 80 to 90 % of patients who present with locally advanced and metastatic pancreatic cancer are even more dismal. Rarely do such patients achieve a complete response to treatment; median survival is 5–10 months and 5-year survival is near zero [2].

There is very little randomised data on adjuvant therapy for pancreatic carcinoma. The ESPAC-1 trial assessed the role of adjuvant therapy in a randomized study. 548 patients were enrolled in Europe in this first large randomized trial. There was evidence that adjuvant chemotherapy brought survival benefits. The five-year survival rate was 21 percent among patients who received chemotherapy [3].

In 1995 a phase II trial was initiated by the Virginia Mason Clinic, Seattle, USA combining pancreaticoduodenectomy and adjuvant therapy with 5-FU, cisplatin, interferon alpha and radiation therapy. Picozzi et al. reported treatment and results in a series of 43 patients with high-risk resected pancreatic adenocarcinoma (84% node positive, 19% margin positive). After a median follow-up period of 32 months the 2-year survival rate was 64% and the 5-year survival rate was 55% [4]. The overall recurrence rate was 12% of which 80% occurred within 2 years after surgery [5].

Since the Virginia Mason group reported such encouraging results in improving survival periods, there has been considerable interest in gaining increased experience with this therapy combination in an effort to confirm results and evaluate the toxicity profile of a modified version of this regimen.

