### Study design

The CapRI study is designed as an open, controlled, prospective, randomised potentially multi-centre trial meant to evaluate the post-operative overall survival of patients with pancreatic adenocarcinoma receiving chemo-radiotherapy including interferon alpha 2b administration compared with adjuvant chemotherapy. The treatment is offered to a heterogeneous group of people under clinical circumstances, covering a wide age range, for both sexes and with heterogeneous characteristics / co-morbidities.

One year after inclusion of the first patient an interim analysis will be performed. If at this time point there is already a significant difference between both groups favouring the Virginia Mason scheme (p < 0.001) group B (5-FU/Folinic acid) will be stopped and replaced by group C (chemoradiation without interferon alpha). This group will help to define the possibly deciding influence of interferon alpha on the effectiveness of the Virginia Mason treatment protocol. Addition of group C to the study would be the matter of a separate study amendment. The study design will not be changed prior to agreement of the ethics committee.

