### Randomisation and standardised treatment scheme

A block-randomisation-list is generated via computer system (SAS Version 8.2, SAS Institute Inc., Cary, USA). The sealed randomisation list is stored in the investigator file. Patients are randomised using sealed opaque envelopes in the independent study centre at the Department of Surgery (Clinical Study Centre – "Klinisches Studienzentrum Chirurgie" – KSC) until informed consent is attained and diagnostic procedures rule out any contra-indication for participation in this trial.

After randomisation and pre-treatment evaluation treatment must begin within 12 weeks of surgery. A port catheter will be placed after informed consent and randomisation will be done within one to two weeks after pancreatoduodenectomy for patients in study arm A. These patients will be treated with 200 mg/m^2^/day 5-FU by continuous intravenous infusion at days 1–38.

Cisplatin – 30 mg/m^2 ^(maximum single cisplatin dose of 60 mg) iv over 60 minutes on days 1, 8, 15, 22, 29, 36 (6 doses). Two to three hours before and after cisplatin administration the patients will receive hydration of at least 2 litres.

Interferon alpha-2b (Intron A) will be administered at a dose of 3 million units subcutaneously three times weekly (Monday, Wednesday, and Friday) for 17 doses. Non-steroidal anti-inflammatory drugs and steroids should be avoided if possible during Intron A treatment.

External beam radiation is to be given concurrently with chemotherapy with a total dose of 50.4 Gy in 28 fractions over 5.5 weeks (1.8 Gy/day). The pancreatic bed (i. e. resection margin) will be covered with a minimum margin of 2 cm. The hepatoduodenal ligament, origins of the celiac axis and superior mesenteric artery will be included. The AP/PA fields must include the entire duodenal C-loop as seen on the pre-operative CT scan. All patients will receive XRT per informed consent. A four-field technique with AP/PA and lateral fields and customised blocking is required. The beams will be weighted more heavily in the AP/PA fields (usually 2:1 compared to the lateral fields). The dose contribution from the lateral fields should be restricted to 20 Gy. Simulation should be done with the patient in the supine position with "arms up" position. A dosage greater than or equal to 10 MV photons should be used.

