### Statistical considerations and sample size estimation

The primary endpoint in this study is the overall survival period, measured from the date of resection. The sample size calculation is based on the assumption of a constant monthly hazard rate of 0.044 in the standard group and a constant monthly hazard rate of 0.021 in the experimental group. The hazard values are derived from two-year survival rates in the study groups (using the formula λ_group _= -1 × ln(P_24,group_)/24) with a two-year survival rate of 35% in the control group [11,12]and a conservative two-year survival rate of 60% in study arm A[13].

Assuming an accrual period of 18 months and a follow-up of 42 months [14,15], testing for a difference in hazard (hazard ratio ≠ 1) on level α = 0.05 and with a power of 80% a study sample size of 96 patients is needed. Taking into consideration the estimate of approximately 14 patients which will not complete the treatment, a total number of 110 patients should be randomised.

The overall survival will be summarised by Kaplan-Meier estimate and differences in therapy protocols will be analysed by univariate Cox-regression.

Various secondary endpoints will be evaluated in this study as well. Disease free survival, measured from date of operation, will be summarised by Kaplan-Meier estimate.

One year after inclusion of the first patient an interim analysis will be carried out which could result in stopping arm B. The planning of the study is based on a fix sample approach and not on groups sequential. Because the alpha level of the interim analysis is set to α = 0.001, the sample size calculated from a group sequential approach will be similar to the sample size of the fixed study approach.

The main evaluation will be performed two years after the last patient's enrolment.

There will be explicit stopping rules in place to terminate the trial early in the unlikely event that an unacceptably high rate of treatment related deaths (TRD) is observed. TRD will be monitored using the design of Thall and Simon [16]. A non-informative Beta prior distribution (i.e., B (0.015, 0.085) for TRD rate is assumed. The trial will be stopped if at any point during the trial there is a greater than 90% probability that the true TRD rate is greater than 0.05. Each patient will subsequently be evaluated and, an independent safety board will be consulted in making decision.

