In view of the poor prognosis of the patient group, there will be no explicit stopping rules based on the overall number of toxicities, since even high rates of reversible toxicities seem acceptable if there is a large survival gain. Patients can withdraw from study participation at any time. Patients are taken off the study if unacceptable toxicity appears. Unacceptable toxicity is defined as unexpected serious side effects or irreversible Grade 4 toxicity. Patients who withdraw from the study may be treated with 5-FU and folinic acid or with gemcitabine. The decision will be based on the individual reasons for withdrawing from the study.

One year after inclusion of the first patient an interim analysis will be done. If at this time point there already is a significant difference between both groups favouring the Virginia Mason scheme (p < 0.001) group B (5-FU/Folinic acid) will be stopped and replaced by group C (chemoradiation without interferon alpha).

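### The one-year interim is justified by patient safety, but its stated rule acts only on a result favouring arm A and attaches no response to worse survival in arm A

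*Protocol article*

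**What the plan says.** **Purpose of the look.** The abstract states: "An interim analysis for patient safety reasons will be done one year after start of recruitment".

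**Rule for the look.** The section on statistical considerations and sample size says: "One year after inclusion of the first patient an interim analysis will be carried out which could result in stopping arm B". It closes with the criterion: "If at this time point there already is a significant difference between both groups favouring the Virginia Mason scheme (p < 0.001) group B" is to be stopped and replaced by group C, chemoradiation without interferon. The Study design section gives the same criterion, direction and threshold. It adds that group C would need a separate amendment and the ethics committee's agreement.

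**Other safeguards.**
- Treatment-related deaths are monitored throughout. The trial stops if there is a "greater than 90% probability that the true TRD rate is greater than 0.05", and "an independent safety board will be consulted in making decision".
- An adverse events committee classifies critical events, and two independent oncologists do the medical monitoring.
- Overall survival follow-up is evaluated once a year (Investigation schedule and follow-up). The text does not say that this is done by arm or who sees it.
- There is deliberately no stopping rule on the overall number of toxicities. The reason given is that a large survival gain would make reversible toxicity acceptable.

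**The concern.** A reader of the abstract would expect the one-year look to protect patients in both arms. As written, it protects patients in arm B from an inferior control treatment. If arm A did worse, no action follows from the look, whatever the p-value.

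An adverse result is conceivable on the article's own account. The Discussion says that the earlier randomised trial favoured chemotherapy over chemoradiation, although it notes that the quality of that chemoradiation is disputed. The primary test is against a hazard ratio different from 1, so it allows for either direction.

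With even accrual of 110 patients over 18 months, 110 × 6/18 ≈ 37 patients, about 18 of them for arm A, are still to be randomised at month 12. The interim is the only between-arm comparison that the article describes before recruitment ends, and its stated rule does not bring an adverse survival result to the safety board.

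**Working it through.** **1. The plan's own figures.** The hazards come from two-year survival: −ln(0.35)/24 = 0.0437 and −ln(0.60)/24 = 0.0213 per month, stated as 0.044 and 0.021. Schoenfeld's formula with hazard ratio 0.487 gives 4(1.960 + 0.842)²/(ln 0.487)² ≈ 61 events. With 18 months of even accrual and analysis at month 42, the event probabilities are 0.758 (B) and 0.502 (A), mean 0.630. So N = 61/0.630 ≈ 97, against 96 stated. The plan's inputs reproduce, and 96 + 14 = 110.

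**2. Information at month 12.** Assumed: even accrual, 1:1 allocation, overall survival as the interim endpoint, follow-up counted from entry. Patients per arm: 110 × 12/18 ÷ 2 = 36.7, so about 73 in all, with mean follow-up of 6 months. The chance of death by the look at hazard λ is 1 − (1 − e^(−12λ))/(12λ).

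| Arm A hazard | Deaths A | Deaths B | Total |
|---|---|---|---|
| 0.021 (design) | 4.3 | 8.2 | 12.4 |
| 0.044 (equal) | 8.2 | 8.2 | 16.4 |
| 0.066 (HR 1.5) | 11.3 | 8.2 | 19.5 |
| 0.088 (HR 2) | 14.0 | 8.2 | 22.2 |

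**3. The existing rule.** Two-sided p < 0.001 in favour of A with 12.4 deaths needs an observed hazard ratio of about exp(−2 × 3.291/√12.4) = 0.15. Simulation puts the chance of crossing under the design at 1.4% if the hazards separate at entry, and at 0.6%, 0.3% and 0.1% if they separate 1.5, 3 or 6 months later. A mirrored p < 0.001 bound for harm would be crossed only about 5% of the time at HR 2, so a useful harm trigger needs a looser level.

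**4. A review trigger at one-sided p < 0.05 against A.** The approximate chance of firing is Φ(√(D/4) × ln HR − 1.645), where D is the number of deaths. At HR 2: √(22.2/4) × 0.693 − 1.645 = −0.01, or about 49%. At HR 1.5: √(19.5/4) × 0.405 − 1.645 = −0.75, or about 23%. Simulation (log-rank test, 40,000 trials per scenario) agrees and extends this to delayed separation:

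| True state | No delay | 1.5 months | 3 months | 6 months |
|---|---|---|---|---|
| HR 2 | 49% | 34% | 22% | 10% |
| HR 1.5 | 22% | 16% | 12% | 7% |
| Arms equal | 5% | 5% | 5% | 5% |
| Design true | 0.2% | 0.5% | 1.3% | 3.0% |

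HR 1.5, HR 2 and the delays are assumptions. Some delay is likely: "After randomisation and pre-treatment evaluation treatment must begin within 12 weeks of surgery", and for patients without adjuvant therapy the Background says "Relapse occurs within 9–15 months after initial presentation".

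**5. What the death rule covers.** With the stated Beta(0.015, 0.085) prior, the 90% boundary is reached at 5 treatment-related deaths in 37 patients (posterior probability 0.968) or 7 in 73 (0.932). It measures deaths classed as treatment-related against a fixed 5% rate. An excess of arm A deaths classed otherwise, for example after earlier recurrence, does not count towards it.

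**The case against.** **Protecting arm B is also a safety reason.** The abstract's phrase does not say whose safety is meant, and a one-directional efficacy boundary is a legitimate choice. This stands. The text does not contradict itself; the rule covers part of the purpose.

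**A condensed article leaves board procedures to the full protocol or charter.** This has some force, since naming one consequence does not exclude others. But the article does not defer the rule. It states it in two sections, both times in the same direction, and it also gives the purpose that the rule only partly meets.

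**Early harm would mostly be toxic death, which is already monitored.** This is the strongest argument, and much of it stands. Suppose that every excess arm A death is classed as treatment-related. At HR 2 without delay, the death rule then fires by month 12 in about 95% of trials if applied to arm A and 64% if pooled, against 49% for the proposed trigger. With a 1.5-month delay the figures are about 80% and 30%, against 34%. At 3 months the pooled rule falls to about 8%, against 22%. The overlap depends on that attribution, and the article does not say whether the rule is applied to arm A or pooled.

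**Survival is evaluated annually anyway.** This shows that survival review is not confined to the p < 0.001 test. It is not described as a comparison by arm or as a report to the board.

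**The trigger has little power.** True with delayed effects: at 6 months it fires in 10% of trials at HR 2, against 5% when the arms are equal.

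A reader might infer that the trial has no safety stopping rule, or that arm A patients are unprotected. The article does not support either: the death rule runs throughout and leads to an independent board.

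**Conclusion.** The point holds as a minor one. The look described as a safety measure has a rule that acts only in favour of arm A, and no response to worse survival in arm A is stated for it. No estimate, error rate or sample size is affected.

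The gain from correcting it is modest: the board would see a comparison that is already planned, about 37 patients before recruitment closes. With 12 to 22 deaths, a formal trigger detects a doubled hazard in about half of trials at best and in 10% if the effect is delayed by 6 months. These figures rest on even accrual, 1:1 allocation, overall survival as the interim endpoint (the article says only a significant difference between groups), and assumed harm effects and delays.

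It would go too far to read the one-sided boundary as an error in itself, or to take the low crossing probabilities as a reason to change it.

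**What to change.** Keep p < 0.001 favouring arm A. Add to the Study design section and to both statements of the interim in the statistical section, for example:

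> At this look, overall survival by arm and the adverse event tables are reported in confidence to the independent safety board. If survival is worse in arm A at a level that the board has fixed beforehand (for example one-sided p < 0.05), the board reviews the trial. The trigger is non-binding and randomisation does not pause automatically. A result short of the trigger is not evidence against harm.

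If the look is meant for efficacy only, reword the abstract and state where worse survival in arm A is examined.

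**Cost.** One paragraph of amendment. The comparison, the tables and the board already exist. A non-binding harm review cannot raise the chance of wrongly declaring arm A better, so the efficacy boundary and the sample size stand. The downside at the 0.05 level is an unneeded review in about 5% of trials if the arms are equal, and in 0.2% to 3.0% if the design is true. In an open trial a review may also signal the interim trend; confidential reporting limits that risk but does not remove it.

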## Discussion

The role of adjuvant therapy in potentially curatively resected adenocarcinoma of the pancreas remains a matter of debate. As the first, large multi-centre randomised controlled trial (RCT), the ESPAC-1-Trial clearly favoured adjuvant chemotherapy over postoperative chemoradiation [3]. However the quality of the radio-chemotherapeutic regimen in the ESPAC-1-Trial has been disputed. The Virgina Mason study group in Seattle, USA, published very promising data in phase-II-study involving immunotherapy and chemoradiation in the adjuvant setting [4]. The reliability of the data has been intensively discussed and there even a source-data-verification was performed by the National Cancer Institute (NCI). In the current setting with a reference adjuvant treatment from an RCT and very promising data from a phase-II-trial, there is the ideal basis for a controlled trial comparing the two most current and successful regimen. Being a centre focusing on pancreatic diseases and especially malignancies we therefore planned and conduct such a trial.

The CapRI study is an open, randomised controlled trial investigating the survival of patients after potentially curative resection of a pancreatic adenocarcinoma treated adjuvant with 5-FU, cisplatin, INTRON A combined with radiation or 5-FU plus folinic acid. The role and the mechanism of interferon alpha 2b in patient's chemoradiation regimen are evaluated. The toxicity, the disease-free interval and the quality of life are assessed. Different factors are tested for a potential role as predictive marker.

The results of the CapRI trial will definitely advance clinical and scientific knowledge on the adjuvant treatment of pancreatic carcinoma as it may confirm or de-mystify the remarkable results from the Virginia Mason study group.

## Abbreviations

CCC Comprehensive Cancer Centre

CRF Case Report Form

CRO Clinical Research Organisation

GCP Good Clinical Practice

ICH International Conference on Harmonisation of Technical

Requirements for Registration of Pharmaceuticals for

Human Use

IEC Independent Ethics Committee

ITT Intention-to-treat-analysis

NCT National Centre for Tumourdiseases

RCT Randomised Controlled Trial

SDGC Study Centre of the German Surgical Society

## Note

Table 1: Investigation schedule

Table 2: Eligibility Criteria
